## Abstract

**Background:**

After spinal cord injury (SCI), a large number of survivors suffer from severe motor dysfunction (MD). Although the injury site is in the spinal cord, excitability significantly decreases in the primary motor cortex (M1), especially in the lower extremity (LE) area. Unfortunately, M1 LE area-targeted repetitive transcranial magnetic stimulation (rTMS) has not achieved significant motor improvement in individuals with SCI. A recent study reported that the M1 hand area in individuals with SCl contains a compositional code (the movement-coding component of neural activity) that links matching movements from the upper extremities (UE) and the LE. However, the correlation between bilateral M1 hand area excitability and overall functional recovery is unknown.

**Objective:**

To clarify the changes in the excitability of the bilateral M1 hand area after SCI and its correlation with motor recovery, we aim to specify the therapeutic parameters of rTMS for SCI motor rehabilitation.

**Methods:**

This study is a 12-month prospective cohort study. The neurophysiological and overall functional status of the participants will be assessed. The primary outcomes included single-pulse and paired-pulse TMS. The second outcome included functional near-infrared spectroscopy (fNIRS) measurements. Overall functional status included total motor score, modified Ashworth scale score, ASIA Impairment Scale grade, spinal cord independence measure and modified Barthel index. The data will be recorded for individuals with SCI at disease durations of 1 month, 2 months, 4 months, 6 months and 12 months. The matched healthy controls will be measured during the same period of time after recruitment.

**Discussion:**

The present study is the first to analyze the role of bilateral M1 hand area excitability changes in the evaluation and prediction of overall functional recovery (including motor function and activities of daily living) after SCI, which will further expand the traditional theory of the predominant role of M1, optimize the current rTMS treatment, and explore the brain-computer interface design for individuals with SCI.

**Trial registration number:**

ChiCTR2300068831.

**Supplementary Information:**

The online version contains supplementary material available at 10.1186/s12883-024-03705-0.

## Introduction

Spinal cord injury (SCI) often occurs in young adults [1]. Although the injury site is in the spinal cord, significantly decreased excitability in the primary motor cortex (M1), especially in the lower extremity (LE) area, has been found in the early stage of SCI [2, 3]. Therefore, targeted regulation of the M1 LE might promote motor recovery. Unfortunately, some studies indicate that even after four weeks of continuous M1 LE area repetitive transcranial magnetic stimulation (rTMS), the gait function of individuals with SCI did not improve significantly compared with that of individuals in the sham group [4, 5]. One possible reason for this may be due to the deep location of the M1 LE area, the small size, and the limited efficacy of the current figure-8, circular rTMS coils [6]. The H-coil is designed to achieve effective stimulation of deep neuronal regions. However, the H-coil is disadvantageous because of its wider electrical field distribution and lower stimulation accuracy in the brain [7]. Therefore, the latest rTMS guidelines do not recommend treating motor dysfunction (MD) after SCI [8]. Identifying new targets of rTMS is a high priority.

Using multiunit recordings, one study reported that the hand knob area of the precentral gyrus (the location of the M1 area) of an individual with SCI is tuned to the entire body. Interestingly, this area contains a compositional code that links matching movements from upper extremities (UE) and LE [9]. The compositional code is the movement-coding component of neural activity and is then transferred to another limb by changing only the limb-coding component. All four limbs movement-coding components could be measured in the M1 hand area. Therefore, the M1 hand area might contain a compositional code that links all four limbs together. Similarly, through precision functional magnetic resonance imaging (fMRI), Gordon EM et al. demonstrated that the classic M1 area is functionally interrupted by regions with distinct connectivity and alternating with effector-specific (foot, hand and mouth) areas [10]. Very recently, Lorach H et al. attempted to restore communication between the brain and spinal cord with a brain–spine interface (BSI) that enabled chronic tetraplegia individuals with SCI to stand and walk naturally. Interestingly, the region that responded more robustly to the intention to move the LE identified by electrocorticography (ECoG) signals basically covered the M1 hand area [11]. According to the classic M1 organization as a continuous homunculus from toe to head, the hand area is shallower and larger than the LE area [12]. Therefore, compared with M1 LE motor-evoked potentials (MEPs), M1 hand area MEPs are more commonly used because of the high detection rate of MEP amplitude in the clinic. Taken together, these findings clarify the changes in the excitability of the bilateral M1 hand area after SCI and its correlation with motor recovery and the ability to perform activities of daily living (ADL). This is of paramount significance for specifying the therapeutic parameters of rTMS for SCI motor rehabilitation.

In our recent study, we explored the correlation between corticospinal excitability (CSE, reflected by the MEP) changes in the bilateral M1 hand area after SCI and overall functional recovery through a cross-sectional study [13]. The results showed that the CSE of the dominant hemisphere (DH) M1 hand area was significantly greater than that of the nondominant hemisphere (NDH) M1 hand area in healthy controls, whereas in individuals with SCI, the opposite phenomenon occurred: patients exhibited a decrease in the CSE of the DH M1 hand area, while the M1 hand area MEP hemispheric CSE conversion was correlated with ADL ability and LE motor function in individuals with SCI. The closer the degree of M1 hand area MEP hemispheric conversion was to that of healthy controls, the better the extremity motor function/ADL ability patients achieved. To verify the phenomenon found in our previous cross-sectional study, we designed this cohort study to confirm the relationship between hemispheric M1 hand area excitability conversion and overall functional recovery with the extension of the course of SCI up to one year through multilevel brain measurements consisting of MEPs for the CSE, paired-pulse transcranial magnetic stimulation (ppTMS) for intracortical excitability and functional near-infrared spectroscopy (fNIRS) for brain network activation.

## Methods

### Study design and setting

The present study is a 12-month prospective cohort study that does not involve intervention and will be carried out between September 2023 and December 2026 at Xijing Hospital, a tertiary academic medical care institution with 3200 beds in Xi’an, China. Neurophysiological and overall functional status data will be collected for these participants. The outcomes will be assessed in healthy controls and individuals with SCI at disease durations of 1 month, 2 months, 4 months, 6 months and 12 months. The Standard Protocol Items: Recommendations for Interventional Trials (SPIRIT) statement 2013 [14] was used as the reporting guideline for this protocol.

### Sample size calculation

The sample size calculation was conducted via PASS 11.0 software based on the results of the MEP in our cross-sectional study [13], which showed that approximately 27% of healthy controls had a greater M1 hand area CSE in the NDH (P2 = 0.26), and approximately 70% of individuals with SCI had a greater M1 hand area CSE in the NDH (P1 = 0.7, R1 = P1/P2). Other parameters were set as follows: a significance level of α = 0.05 (two tails), power (1–β) = 90%, and standard deviation = 1. Therefore, a sample size of 25 individuals with SCI and 25 healthy controls was used. Considering the dropout rate in the cohort study, as the number of subjects increased by 20%, a minimum of 60 participants (30 individuals with SCI and 30 healthy controls) were needed.

### Participants

#### Inclusion and exclusion criteria

The inclusion criteria for individuals with SCI were as follows: (a) 18–75 years old, right-hand dominant (Edinburgh Handedness Inventory); (b) diagnosed with SCI [15]; (c) stable MEP in the M1 hand area was detectable; (d) no cognitive impairment (Mini-Mental State Examination score ≥ 24) [16]; (e) disease course ≤ 1 month (from SCI onset to first assessment); and (f) agreed to participate in this study and signed the informed consent form. Exclusion criteria: (a) serious nervous system disease, unable to tolerate relevant tests; (b) upper limb fracture, arteriovenous fistula or other diseases leading to movement disorder; (c) ferromagnetic implants in the head or neck; (d) implantation of a cardiac pacemaker; (e) severe coagulation disorder, severe cardiac insufficiency or uncontrollable hypertension: systolic blood pressure > 160 mmHg or diastolic blood pressure > 100 mmHg; (f) other serious systemic diseases such as tumors; (g) taking drugs that may affect the TMS examination within a week, including baclofen, diazepam and other drugs [17]; (h) absolute contraindications for TMS examination.

The inclusion criteria for healthy controls were as follows: (a) 18–75 years old, right-hand dominant (Edinburgh Handedness Inventory); and (b) stable MEPs. Exclusion criteria included the above situations in which TMS could not be performed.

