#### Recruitment and sample selection

Potential participants will first be screened by nurses based on inclusion and exclusion criteria and informed about the study during a consultation with nurses if they meet the inclusion criteria. To assess the external validity of the recruited sample of participants, age and gender will be collected for those participants who refuse to participate in the study [18]. If potential participants are interested in participating in this study, their names will be placed on a trial list. The investigator will contact the participants and explain the procedure. If the participants agree, an informed consent form will be sent. If the participants have any questions, they can contact the investigator.

Upon receipt of the signed informed consent form, the participants will be registered in the electronic case report form (eCRF), and the basic information will be recorded at baseline. Then, the doctor will assess the neuroelectrophysiology data, and the ability to perform ADLs and motor function will be evaluated by an occupational therapist. The participants received a reminder or were contacted by phone at subsequent testing time points. Measurements are recorded by the nurse specialist in the Electronic Patient Record.

After recruitment, individuals with SCI will be measured at disease durations of 1 month, 2 months, 4 months, 6 months and 12 months, including single pulse TMS (spTMS) to evaluate the CSE in bilateral M1 hand areas, ppTMS to evaluate the intracortical excitability in bilateral M1 hand areas, and fNIRS to evaluate bilateral M1 hand area blood flow. All subjects will receive an assessment scale. The matched healthy controls will be measured during the same period after recruitment (flow chart, Table 1).

**Table 1 Tab1:** SPIRIT-figure of the measurement instruments and time of assessment

		Study period						
		Enrolment						
Timepoint	Type	Healthy control	1 month (SCI-T1)		2 months (Control/SCI-T2)	4 months (Control/SCI-T3)	6 months (Control/SCI-T4)	12 months (Control/SCI-T5)

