### Outcome measures

#### Primary outcome

##### spTMS

To evaluate the changes in the M1 hand area CSE between individuals with SCI and healthy controls, the amplitude of the MEP and the resting motor threshold (RMT) will be detected through spTMS equipment (MEP-9404 C, Japan).

The MEP of the M1 hand area was recorded by the magnetic stimulation coil placed in the M1 hand area on the left side of the skull. The recording surface Ag-AgCl electrode and reference electrode were pasted on the abdomen of the abductor pollicis brevis muscle of the right hand and connected to the recording equipment. A single-pulse TMS is delivered to the hotspot under 80% of the maximum stimulator output. The MEP latency and amplitude of the abductor pollicis brevis muscle were recorded. RMT is defined as the minimal amount of stimulus intensity producing MEP peak-to-peak ≥ 50 µV in at least 5 out of 10 consecutive tracks [19]. The protocol used for the right M1 hand area was the same as that described above (Fig. 1A).

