#### MEP and hemispheric excitability conversion degree

The MEP amplitudes of patients and controls will be analyzed by nonparametric tests. The MEP latency and central motor conduction time (CMCT) are analyzed with independent samples *t* tests. The hemispheric excitability conversion degree [ln(DH/NDH ratio)] [13] is compared with generalized estimating equations (GEEs) [27] with respect to disease course (1 m, 2 m, 4 m, 6 m, and 12 m). **P* < 0.05 was regarded as a significant difference.

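### SCI patients must have a detectable hand-area MEP in the first month, so entry is selected on the primary outcome while the conclusions are framed for SCI in general

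*Protocol article*

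**What the plan says.** All places are in the protocol article.

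- **Aim** (Abstract, Objective): "To clarify the changes in the excitability of the bilateral M1 hand area after SCI and its correlation with motor recovery". The population is SCI, without restriction.
- **Eligibility** (Inclusion and exclusion criteria): any diagnosed SCI qualifies ("b) diagnosed with SCI [15"), with entry early ("e) disease course ≤ 1 month (from SCI onset to first assessment") and only if "c) stable MEP in the M1 hand area was detectable". Whether one hemisphere or both must respond is not stated. Controls must also have stable MEPs.
- **Primary outcome** (spTMS): "the amplitude of the MEP and the resting motor threshold (RMT) will be detected through spTMS equipment".
- **Derived measure** (MEP and hemispheric excitability conversion degree): the log of the dominant-to-nondominant amplitude ratio, introduced as "The hemispheric excitability conversion degree [ln(DH/NDH ratio" and compared over the five time points by GEE.
- **Background** (Introduction): "significantly decreased excitability in the primary motor cortex (M1), especially in the lower extremity (LE) area, has been found in the early stage of SCI". The Introduction also reports, from the group's earlier cross-sectional study, lower dominant-hemisphere (DH) excitability in SCI. The Discussion attributes the weaker cervical result to damage to the upper-limb corticospinal pathway.
- **People not enrolled** (Recruitment and sample selection): to judge external validity, "age and gender will be collected for those participants who refuse to participate in the study". The article mentions no data on patients excluded for an absent MEP.

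**The concern.** The entry rule uses the quantity the study sets out to describe. An SCI patient whose hand MEP has disappeared by the first assessment has the largest possible amplitude loss and no definable RMT, and cannot enter. Any later return of that MEP is never observed. A healthy person almost always passes the same test, so the cut falls on one group only.

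Two consequences follow. First, the cervical subgroup contains only patients whose hand pathway is spared enough to give a response, although injury level is one of the factors the correlation analysis is meant to examine. Second, the log ratio has no value when one side is silent, so the most asymmetric patients cannot contribute to the conversion analysis. What is at stake is the description of change after SCI, and the claim under Clinical and research implications that early excitability may help predict recovery in people with SCI generally.

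**Working it through.** **1. The plan's own figure.** Inputs from Sample size calculation: P1 = 0.70, P2 = 0.26, two-sided α = 0.05, power 90%. Pooled two-proportion formula:

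n = [1.960·√(2 × 0.48 × 0.52) + 1.282·√(0.70 × 0.30 + 0.26 × 0.74)]² / 0.44² = (1.385 + 0.813)² / 0.1936 = 24.95, so 25 per group, with power 90.1%. The stated 25 reproduces. The point does not rest on a sample-size error.

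**2. Which patients the ratio loses.** ln(DH/NDH) goes to −∞ as DH → 0, to +∞ as NDH (nondominant) → 0, and is undefined when both are absent. If the criterion means both sides, patients with one silent side are lost at entry. If it means one side, they enter but drop out of the ratio. Complete cases for the ratio at the first assessment are the same patients under either reading.

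**3. Amplitude-floor simulation.** Every parameter is an assumption: normal median 2 mV, detection floor 50 µV, log-SD 1.0 (first two rows) or 1.2 (last two), correlation 0.5 between sides, mean ln ratio about −0.52 in all SCI. A control falls below the floor only at ln(2/0.05)/1.0 = 3.69 SD (3.07 SD with log-SD 1.2), which is 0.1% or less. Both MEPs are required.

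| SCI lacking an MEP on ≥ 1 side | Lacking both | Mean DH log-amplitude loss, all → selected | Change | Mean ln ratio, all → selected |
|---|---|---|---|---|
| 3% | 0.2% | 1.76 → 1.69 | −4% | −0.52 → −0.50 |
| 9% | 1% | 2.26 → 2.09 | −8% | −0.52 → −0.48 |
| 27% | 6% | 2.76 → 2.27 | −18% | −0.52 → −0.41 |
| 44% | 14% | 3.26 → 2.51 | −23% | −0.53 → −0.37 |

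Take the control mean ratio as Φ⁻¹(0.73) = 0.613, from the 27% in the text. The group difference then falls from 1.138 to 1.088 with 9% missing (−4%) and from 1.135 to 1.025 with 27% missing (−10%; −9% if the control mean is rescaled to the larger SD). With 3% missing it falls by 2%.

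**4. Worst-case truncation.** Suppose the missing patients are exactly the lowest-ratio tail of SCI. SCI mean = Φ⁻¹(0.30) = −0.524, so the difference is 0.613 + 0.524 = 1.137 SD. Removing the lowest share q raises the SCI mean by φ(z_q)/(1 − q). The observed P1 becomes (0.70 − q)/(1 − q). Power is at 25 per group against 0.26.

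| q (assumed) | Shift | Difference | Change | P1 | Power |
|---|---|---|---|---|---|
| 5% | 0.109 | 1.03 SD | −10% | 0.684 | 88% |
| 10% | 0.195 | 0.94 SD | −17% | 0.667 | 84% |
| 20% | 0.350 | 0.79 SD | −31% | 0.625 | 75% |

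**5. Direction of the ratio.** Let s be the share of missing patients who have the DH as the weaker side: P1 observed = (0.70 − q·s)/(1 − q). At q = 20%, s = 1.0 gives 0.625, s = 0.7 gives 0.700 (no change), and s = 0.5 gives 0.750. The sign depends on s, which the documents do not give.

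**The case against.** - **The direction for the ratio is not established.** This stands. A reader might infer that the hemispheric conversion is understated. The Introduction reports lower DH excitability on average, not which side loses its MEP, and step 5 shows that the effect can vanish or reverse.
- **The 17% and 31% figures are extremes.** This stands. Absence depends on amplitude, not on the ratio, so the two sets of patients overlap only in part. The simulation gives much smaller effects at similar shares.
- **The 70% may already come from patients with detectable MEPs.** This stands. It is taken from an MEP-based study that is not shown. If that study applied the same filter, truncating again counts the selection twice and planned power is unaffected. A reader might infer that the study is underpowered; the documents do not support that.
- **A detectable MEP is a measurement need.** This stands. Paired-pulse indices are expressed relative to a baseline MEP, so the criterion itself is no error.
- **An absent hand MEP may reflect tract damage rather than low cortical excitability, and the Introduction says the early fall is mainly in the lower-extremity area.** This is fair, and it limits what absence can be said to mean. It does not alter the selection on amplitude and RMT, which are the named outcomes.
- **The article speaks throughout of the bilateral hand area, so both sides are probably meant.** That is plausible but not written, and under either reading the ratio loses the same patients at entry (step 2).
- **Scoring lost MEPs and logging screening failures are commonly left to a full protocol or SAP.** This is true, and their absence alone would be no finding. It is also unknown whether exclusions are logged elsewhere. What the article does fix is the entry rule, the log ratio and the unrestricted population, and these do not fit together. Nonparametric tests on raw amplitude could rank an absent response lowest; the log ratio has no such place for it.

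**Conclusion.** The point holds for amplitude and RMT. Entry is conditioned on the primary outcome in the first month, the cut falls almost wholly on the SCI group, and the SCI–control difference is likely understated. In the simulation the loss of DH log-amplitude is understated by 4% with 3% of patients missing and by 18% with 27% missing. The cervical subgroup describes only patients with a spared hand pathway.

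For ln(DH/NDH), what holds is that patients with one silent side cannot contribute. The bias runs toward controls only if absence is mainly on the dominant side. Its size is unknown because the share without an MEP is not given. Under the assumed shares it runs from about 2–10% (simulation, 3–27% missing) to 31% (worst-case truncation at 20%). It could be negligible if few patients lack a hand MEP.

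The main consequence is that conclusions framed for individuals with SCI are broader than the enrolled population can support.

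**What to change.** 1. State whether the MEP criterion requires a response on one side or both.
2. Limit the conclusions to SCI with a preserved hand-area MEP in the first month.
3. Keep visits with a one-sided absent MEP in the conversion analysis, either as the extreme rank or as a value censored below the recording's detection limit. The 50 µV in the spTMS section is the RMT criterion, not an amplitude detection limit, so use it only as a stated assumption. Give a rule for bilateral absence, and report complete cases as a sensitivity analysis.
4. For SCI patients excluded under the criterion, log their number, injury level, AIS grade and the side or sides without a response.

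The criterion can remain. The cost is a few screening-log items and some wording, a floor or rank assumption for absent responses, and a narrower claim. These changes do not recover the patients screened out; they make the selection visible and match the claim to the sample.

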#### Correlation analysis and multiple linear regression analysis

Correlation analysis of hemispheric excitability conversion degree and overall functional recovery was performed to determine the effects of disease course, AIS grade, and neurological level of injury. Pearson correlations between different phases/groups were calculated after the normality test. **P* < 0.05 is regarded as a significant difference.

Univariate and multivariate linear regression analyses will be conducted to validate the influence of hemispheric excitability conversion degree as an independent factor. The MBI and SCIM are set as the linear regression analysis outcomes. The inclusion criterion for univariate analysis was *P* < 0.10. **P* < 0.05 is regarded as a significant difference.

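### The entry rule allows the first assessment at any time up to 1 month after injury, yet that assessment is scheduled, labelled and analysed as the 1-month visit

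*Protocol article*

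**What the plan says.** Among the patient inclusion criteria, in *Inclusion and exclusion criteria*, is "e) disease course ≤ 1 month (from SCI onset to first assessment". The clock starts at injury and stops at the first assessment. There is a maximum and no minimum.

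The schedule is stated differently. *Study design and setting* has outcomes assessed "at disease durations of 1 month, 2 months, 4 months, 6 months and 12 months". *Recruitment and sample selection* says that, after recruitment, "individuals with SCI will be measured at disease durations of 1 month, 2 months, 4 months, 6 months and 12 months". Table 1 labels the first patient visit 1 month (SCI-T1), and puts the eligibility screen, consent and all the first measurements in that one column.

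*Recruitment and sample selection* also gives the order of events. Signed consent is followed by registration and recording of basic information, and then: "Then, the doctor will assess the neuroelectrophysiology data". Function and ADL scoring are part of the same step, and reminders are sent for the later test points.

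In the analysis, the hemispheric conversion degree is compared by GEE "with respect to disease course (1 m, 2 m, 4 m, 6 m, and 12 m". The section on correlation and regression relates conversion degree to functional recovery "to determine the effects of disease course, AIS grade, and neurological level of injury", with Pearson correlations by phase and group.

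**The concern.** Disease course is the main axis of this study. It defines the visits, it is the time factor in the GEE, and it is one of the factors examined in the correlations. If the first category on that axis can hold patients at very different times after injury, two results become harder to read.

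- **The first step of the time course.** The T1 mean would describe a mixture of days since injury, and the difference between the first two categories would cover a different elapsed time in each patient.
- **The correlations at T1.** If both conversion degree and function change with days since injury in the first month, patients tested later would tend to differ on both. Part of the correlation between them could then come from the day of testing. The planned patient group is small (25 by calculation, 30 after allowing for dropout), so there is little room to absorb this.

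**Working it through.** No figure in the article underlies this point. The check sets the passages side by side and then works out the range that they permit.

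**1. Do the entry rule and the schedule agree?**

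| Source | Timing of the first assessment |
|---|---|
| Inclusion criterion (e) | Any time from injury up to 1 month |
| Study design and setting | Disease duration of 1 month |
| Recruitment and sample selection, schedule sentence | Disease duration of 1 month, after recruitment |
| Recruitment and sample selection, order of events | After consent and registration, with no instruction to wait |
| Table 1 | 1 month (SCI-T1), same column as screening and consent |
| GEE | Nominal category, 1 month |

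Taken literally, criterion (e) and a visit at 1 month meet only at the boundary. A first assessment at two weeks satisfies (e) but is not a 1-month visit. If T1 were given a window on both sides of 1 month, the later half of that window would fail (e).

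**2. What range does the wording permit?**

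Assumptions, not in the article: a month is 30 days, and T2 takes place on day 60.

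Gap from T1 to T2 = 60 − day of first assessment.

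| Day of first assessment | T1-T2 gap (days) |
|---|---|
| 1 | 60 − 1 = 59 |
| 7 | 60 − 7 = 53 |
| 14 | 60 − 14 = 46 |
| 21 | 60 − 21 = 39 |
| 30 | 60 − 30 = 30 |

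The nominal gap is 30 days. The longest permitted gap is 59 days, and 59 / 30 = 1.97, so the interval can nearly double under the same label.

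**3. Does the analysis text correct for this?**

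The article names the nominal times for the GEE and does not mention days since injury. It does not say that actual dates will be ignored. Checking criterion (e) requires the injury date and the date of the first assessment, so the data for a correction must already be collected.

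**The case against.** The strongest reply is that the article fixes T1 at 1 month several times, and that an eligibility limit should not override a schedule. On this reading (e) only keeps out later-stage patients, recruitment comes first, and T1 is then done at 1 month. The term first assessment is not defined as T1 either. It could mean screening, since a stable MEP and a cognitive score are needed for eligibility. This reading is possible, and under it no mixing occurs. It is not what (e) says, however: the criterion counts to the first assessment and not to enrolment, Table 1 has no separate screening column for patients, and the order of events runs from consent into baseline testing. Staff could reasonably follow either reading.

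A second reply is that visit windows and the choice between actual and nominal time usually belong in the full protocol or analysis plan. That stands for their absence alone. The finding is that the stated entry rule and the stated schedule disagree. The window and the use of actual days are remedies.

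Three stronger readings are tempting, and the article does not support them.

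- **The controls run on a different clock.** A reader might infer from Table 1 that controls wait 2 months for their second test while patients wait 1. But the text says "The matched healthy controls will be measured during the same period after recruitment", and the shared control and patient columns fit equal intervals at least as well.
- **The size of the distortion can be calculated.** That would need a recovery curve (such as recovery in log time) and a distribution of test days (such as an even spread over the month). The article gives neither, nor does it say how fast a between-hemisphere log ratio drifts from day to day.
- **T1 anchors every analysis.** No change-from-T1 endpoint or T1-T2 contrast is specified, the GEE uses all five times, and early prediction appears only as an implication in the Discussion.

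**Conclusion.** The inconsistency is real and should be corrected. Criterion (e) permits a first assessment at any time up to 1 month, while the schedule, Table 1 and the GEE treat that assessment as the 1-month point. On the assumptions of a 30-day month and T2 on day 60, the first category may span the first days to about day 30 after injury, with a T1-T2 gap of 30 to 59 days.

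This is what the wording allows and not a prediction. If all patients are in fact tested close to 1 month, the effect is negligible. If many are recruited and tested early, it matters. The article does not give the timing of recruitment. A distorted T1 correlation also requires that both excitability and function change with days since injury within the first month, which is plausible but not shown. The later visits and the control comparison are not affected on the evidence in the article.

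**What to change.** 1. Reconcile criterion (e) with the T1 schedule. Make (e) a limit on the time from injury to enrolment, and hold T1 in a stated window around 1 month after injury, whatever the day of consent. Put the same definition in the design text and Table 1.
2. Whether or not the wording is changed, use actual days since injury as the time variable in the GEE and as a covariate in the T1 correlations.
3. Report the distribution of days from injury to T1, so that readers can see how far the tests spread.

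The cost is low. The change is to wording, scheduling and the model specification, and no extra patients are needed. The downside is that patients enrolled early wait for T1. Because eligibility requires a detectable stable MEP, some may also need that check at enrolment, ahead of T1. For patients already tested, the analysis needs only the injury date and the test dates.
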